### Chemotherapy

Adjuvant PCV chemotherapy is per standard of care, which in the UK is usually according to the BR12 trial schedule.^19^ Chemotherapy should start within 4–8 weeks of completion of RT. Initial doses (in the absence of renal or hepatic impairment) will be as follows:

Procarbazine 100 mg/m^2^, with dose banding/capping as per the institution’s usual practice one time per day on days 1–10 or days 2–11, orally, on a 42 day cycle, for up to six cycles.Lomustine 100 mg/m^2^, with dose banding/capping as per the institution’s usual practice day 1, orally, on a 42 day cycle, for up to six cycles.Vincristine 1.4–1.5 mg/m^2^ (or flat dose of 2 mg if this is usual institutional practice), with dose banding/capping as per the institution’s usual practice, intravenously, day 1, on a 42 day cycle for up to six cycles.

Suggested dose modifications and reductions are provided in the APPROACH trial protocol regarding PCV in the presence of haematological, pulmonary or neurological toxicity or renal or hepatic dysfunction.

### Endpoints

#### Primary endpoint

The primary outcome is NCF assessed at baseline and at 1, 12, 24, 36, 48 and 60 months post-RT. NCF will be measured by the paper-based European Organisation for Research and Treatment of Cancer (EORTC) Core Clinical Trial Battery Composite (CTB COMP).^20 21^ CTB COMP evaluates processing speed, verbal memory and executive functioning.

The CTB COMP consists of the following tests, yielding six measures:

Hopkins Verbal Learning Test-Revised (HVLT-R) consists of three parts: free recall, delayed recall and delayed recognition. It measures various aspects of verbal learning and memory, namely storage of verbal information as well as active and passive retrieval of this information.Trail Making Test (TMT part A and TMT part B). Part A indexes visual-motor scanning speed, while part B assesses executive functioning.Controlled Oral Word Association test (COWA) measures expressive language.

The primary endpoint will be the difference in NCF scores, measured by CTB COMP, between the PBT and photon RT arms at 5 years post-RT.

#### Secondary endpoints

Secondary endpoints are shown in table 3.

**Table 3 T3:** Secondary endpoints

Endpoint	Definition/measurement
Additional NCF tests	Computer-based CNS Vital Signs platform, which evaluates attention, psychomotor speed, verbal/visual memory and aspects of executive functioning^44^
Caregiver distress	Caregiver needs screen
Work and economic impact (participants and carers)	WPAI: General Health Questionnaire, and Health Resource Use Questionnaire
Treatment compliance	Total dose of RT delivered; overall treatment time; details of any interruptions to RT and reasons; delivery of any fractions using photon RT instead of PBT; number of chemotherapy cycles; chemotherapy doses delivered; details of any modifications and reasons
Endocrinopathies	Static/dynamic testing of the following on blood samples: GH/IGF-1 FSH/LH Testosterone and SHBG (male participants) Oestradiol (female participants) Cortisol Free T3/T4, TSH Prolactin
Safety and toxicity	Acute (≤3 months post-RT) and late (>3 months post-RT) toxicities measured using CTCAE V.5.0.
HRQoL	EORTC QLQ-C30 and BN20, EQ-5D-5L, MFI and HADS.
Tumour response assessment	MRI brain performed with the following sequences: • T2 • FLAIR • DWI • T1 pregadolinium T1 postgadolinium Evaluation based on RANO criteria.
PFS	Time from randomisation to the date of the first-documented evidence of progression or death from any cause.
OS	Time from randomisation to the date of death from any cause.

CNScentral nervous systemCTCAECommon Terminology Criteria for Adverse EventsDWIdiffusion-weighted imagingEORTC QLQ-C30 and BN20European Organisation for Research and Treatment of Cancer Quality of Life Questionnaire and Brain Neoplasm QuestionnaireEQ-5D-5LEuroQol-5 Dimension-5 Response-Level QuestionnaireFLAIRfluid-attenuated inversion recoveryFSHfollicle stimulating hormoneGHgrowth hormoneHADSHospital Anxiety and Depression ScaleHRQoLhealth-related quality of lifeIGF-1insulin like growth factor 1LHleutinising hormoneMFIMultidimensional Fatigue AssessmentNCFneurocognitive functionOSoverall survivalPBTproton beam therapyPFSprogression-free survivalRANOresponse assessment in neuro-oncologyRTradiotherapySHBGsex hormone binding globulinTSHthyroid stimulating hormoneWPAIWork Productivity and Activity Impairment

### Statistical considerations

#### Sample size

The primary endpoint of NCF at 5 years will be measured by calculating the mean of standardised z-scores from the HVLT-R, TMT-A/B and COWA components of CTB COMP. A Cohen’s d of 0.5 is regarded as a moderate effect size, which is considered to be clinically relevant given that even small deteriorations in NCF are likely to be impactful in this patient population.^22^ This CTB COMP score is also being used as the primary endpoint measure in the ongoing US NRG-BN005 trial of PBT versus photon RT for cognitive preservation in IDH mutant grade 2/3 glioma (Clinicaltrials.gov NCT03180502). Based on a two-sample t-test with 5% two-sided significance and 90% power, 172 participants (86 per arm) are required to detect an effect size of 0.5. Assuming 30% loss to follow-up at 5 years, 123 participants will be required per arm. The required sample size is therefore 246 participants, to be recruited over 3.5 years. The study is designed with an intermediate and final primary endpoint, whereby a significant positive treatment effect on either endpoint would warrant change in practice. Following the Food and Drug Administration (FDA) guidance on multiple endpoints in clinical trials, the family-wise error rate of 0.05 will be preserved using the fall-back method,^23^ with alpha of 0.01 allocated to the intermediate and 0.04 allocated to the final primary endpoint. Should a significant effect be observed on the intermediate endpoint, the full alpha of 0.05 will be used for the final primary endpoint analysis. Irrespective of the early interim assessment outcome, the trial will continue. Assuming the same sample size calculation, using a type I error of 0.04 (5 years) would provide ~89% power. At the 2 year time point, assuming a smaller dropout rate of 10%, a type I error of 0.01 would provide ~87% power.

#### Randomisation

A computer-generated minimisation programme that incorporates a random element will be used to ensure the treatment groups are well balanced for the following factors:

Histological tumour grade (2 or 3)Tumour size (<5 cm or ≥5 cm)Extent of most recent surgery (biopsy only, subtotal resection or gross total resection)Randomising siteSex

Randomisation will be performed centrally via University of Leeds Clinical Trials Research Unit (CTRU) automated 24-hour randomisation system. The registration and randomisation process will be instigated by onsite research staff; participant consent form must be attained prior to registration (see online supplemental material).

#### Statistical analyses

The trial will be analysed in stages. A detailed statistical analysis will be written before any analysis is undertaken, including interim and final. Statistical analysis will be conducted by the CTRU.

Stage 1: the feasibility of recruitment (numbers of sites opened and participants recruited) will be assessed after the first 12 months. Prespecified traffic light targets will guide assessment of stage 1.^24^ If ≥57 participants are recruited (green), the trial will continue immediately to stage 2. If 37–56 participants (amber) are recruited, barriers to recruitment and remedial action will be explored to inform future trial feasibility. If fewer than 37 participants are recruited (red), a full review of the feasibility of the trial will be undertaken with potential trial closure.

Stage 2: interim analysis of 2 year NCF once all participants have reached ≥2 years follow-up. Stage 2 will analyse early evidence of efficacy, defined by a clinically relevant difference in NCF (Cohen’s d effect size of ≥0.5) between participants treated with PBT and photon RT, using a 1% significance level to account for multiple testing.^25^ The trial will continue to stage 3, regardless of stage 2 results.

Stage 3: further interim analysis of NCF once 50% of participants have reached 5 years follow-up to assess futility. Conditional power will be used to evaluate the probability of achieving a statistically significant result for the final analysis of the primary endpoint, based on accumulated data. A predefined non-binding stopping boundary will be determined in collaboration with the Data Monitoring and Ethics Committee (DMEC) prior to the analysis.^26^

Stage 4: final analysis of primary endpoint of NCF at 5 years and all secondary endpoints.

##### Primary endpoint

The primary endpoint will be assessed on an intention to treat population, including all randomised participants, in the treatment arm they were randomised to. Summary statistics will be presented for NCF scores at each timepoint (baseline and at 1, 12, 24, 36, 48 and 60 months post-RT). A mixed-effects repeated measures model will be used to evaluate differences in mean NCF scores between the two treatment arms. The model will adjust for minimisation factors, baseline NCF score, timepoint, treatment group and treatment group by timepoint interaction as fixed effects. Participant and participant time interaction will be fitted as random effects, as appropriate. The final estimated treatment effect will be reported with 95% CIs and associated significance level. Additional 96% (4% level) CIs will be reported if there is no significant effect at the interim analysis (stage 2). The effect size, accounting for SD, will also be estimated in line with the sample size assumptions.

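### The primary mixed model gives baseline NCF one slope for all visits and leaves the within-participant covariance open, which can cost precision and, in one permitted form, understate the standard error at 60 months

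*Protocol article*

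**What the plan says.** Under Endpoints, Primary endpoint, the article defines the outcome schedule ("The primary outcome is NCF assessed at baseline and at 1, 12, 24, 36, 48 and 60 months post-RT") and then the endpoint itself: "The primary endpoint will be the difference in NCF scores, measured by CTB COMP, between the PBT and photon RT arms at 5 years post-RT". There are thus six post-RT visits, and the confirmatory comparison is at the last of them.

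Under Statistical analyses, Primary endpoint, a mixed-effects repeated measures model is specified. Its fixed part is: "The model will adjust for minimisation factors, baseline NCF score, timepoint, treatment group and treatment group by timepoint interaction as fixed effects". One interaction is named, and it is not baseline by timepoint. Its random part is: "Participant and participant time interaction will be fitted as random effects, as appropriate". The text does not say whether time in the random part is linear or categorical, and it names no residual covariance and no method for standard errors.

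Under Sample size, the calculation is a two-sample t-test without baseline adjustment, for a standardised difference of one half ("Based on a two-sample t-test with 5% two-sided significance and 90% power, 172 participants (86 per arm) are required to detect an effect size of"), then inflated: "Assuming 30% loss to follow-up at 5 years, 123 participants will be required per arm". The error rate is split "with alpha of 0.01 allocated to the intermediate and 0.04 allocated to the final primary endpoint", with the statement that the family-wise rate of 0.05 is preserved.

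Under Statistical analyses, the article says that a detailed analysis plan will be written before any interim or final analysis.

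**The concern.** There are two separate weaknesses in a model whose purpose is to test a single late contrast.

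First, with one baseline coefficient, all six visits share in estimating the slope, and the pooled value is then applied at 60 months. If baseline predicts the 1-month score better than the 5-year score, the adjustment at 60 months is too steep and leaves variance behind. A weakening link is plausible, because late decline after radiotherapy is the premise of the trial, but the article reports no figure for it.

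Second, there is one composite score per visit. An independent participant-by-visit effect therefore cannot be separated from residual error. In practice the wording can mean a linear random slope (a restricted covariance shape), participant-by-visit effects with free covariance (in effect unstructured), or no such term at all. These choices give different standard errors for the same 60-month contrast. At stake are some precision and, under the third choice, the type I error rate of the final test.

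**Working it through.** **The plan's own figures.** n per arm = 2(1.960 + 1.282)²/0.5² = 84.1, so 85 by the normal approximation and 86 by the exact t calculation. 86/0.70 = 122.9, so 123 per arm and 246 in total. Power at alpha 0.04 is Φ(0.5·√(86/2) − 2.054) = Φ(1.225) = 0.890, against the article's "using a type I error of 0.04 (5 years) would provide ~89% power". At 2 years, with 110 per arm and alpha 0.01: Φ(0.5·√(110/2) − 2.576) = Φ(1.132) = 0.871, against about 87%. All of these reproduce.

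**Set-up.** From the article: 246 participants, 1:1 allocation, visits at 1, 12, 24, 36, 48 and 60 months, 30% loss by 60 months, alpha 0.04. Assumed: loss is monotone and completely at random; baseline SD is 1; correlation with baseline (ρ) and SD change linearly over the visits. Post-RT correlations are 0.7 throughout in case A. In the other cases they decay with the gap g in years: 0.3 + 0.55·0.85^g (B, C), 0.2 + 0.65·0.80^g (D), 0.1 + 0.75·0.75^g (E). Results are large-sample; each working model is fitted by minimising its expected Gaussian likelihood criterion.

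**Step 1: cost of the common slope.** The true slope at visit k is b_k = ρ_k·SD_k/SD_0. With a pooled slope β, the approximate variance excess at 60 months is (b_60 − β)²/[SD_60²(1 − ρ_60²)]. In case B: (0.500 − 0.684)²/0.75 = 0.0339/0.75 = 4.5%. The full calculation uses unstructured covariance in both models. Power is at alpha 0.04 for d = 0.5 in units of the 60-month SD.

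| Case (ρ with baseline; SD, 1 to 60 months) | b_60 | β | Variance excess | Power, visit slopes | Power, common slope |
|---|---|---|---|---|---|
| A: 0.6 constant; SD 1 | 0.60 | 0.600 | 0.0% | 99.0% | 99.0% |
| B: 0.75 to 0.5; SD 1 | 0.50 | 0.684 | 4.6% | 97.3% | 96.7% |
| C: 0.75 to 0.5; SD 1 to 1.3 | 0.65 | 0.739 | 0.6% | 97.3% | 97.2% |
| D: 0.8 to 0.4; SD 1 to 1.5 | 0.60 | 0.788 | 1.9% | 95.2% | 94.9% |
| E: 0.8 to 0.3; SD 1 | 0.30 | 0.685 | 15.5% | 93.2% | 89.3% |

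The slope drives the loss, not the correlation alone: a rising SD offsets a falling correlation (B against C).

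**Step 2: standard error from the random effects.** With r = model SE/true SE, the actual two-sided size at nominal 0.04 is 2[1 − Φ(2.054·r)]. For B with a random intercept only: 2[1 − Φ(2.054 × 0.863)] = 0.076.

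| Case | Intercept + linear slope: r, size | Intercept only: r, size |
|---|---|---|
| A | 1.000, 0.040 | 1.000, 0.040 |
| B | 1.042, 0.032 | 0.863, 0.076 |
| C | 0.993, 0.042 | 0.776, 0.111 |
| D | 0.970, 0.046 | 0.713, 0.143 |
| E | 1.051, 0.031 | 0.816, 0.094 |

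All of Step 2 uses the common baseline slope. With intercept plus slope, power in case E is 86.8%.

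**Step 3: family-wise rate.** The final test is run at 0.04 or, after a significant 2-year result, at 0.05. The family-wise rate is therefore at least the actual size of the final test at nominal 0.04. With the intercept-only model in cases B to E that is 0.076 to 0.143, above 0.05 before the 2-year test is counted.

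**Other assumed covariances.** Across a wider set, the common slope costs about 0-6% in most cases and 12-23% under strong decay with equal SDs. Intercept plus slope has size about 0.027-0.047 when SDs change steadily, and 0.07-0.10 only if the SD jumps at 60 months. Intercept only has a standard error about 12-29% too small, with size about 0.07-0.14.

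**The case against.** The strongest reply is that this is analysis-plan detail. The article is condensed, promises a full plan before any analysis, and qualifies its random effects. Covariance structure, degrees of freedom and convergence rules are usually settled there, and baseline as a main effect is conventional. This stands in part: silence on those details is no fault, and an unstructured covariance is compatible with the stated model class. It does not answer the fixed-effects list, which is explicit and which a later plan would naturally carry over, or a random part whose permitted readings include an anti-conservative one.

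Several stronger readings are tempting, and the documents do not support them:

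- That precision is certain to be lost. The loss is zero when the slope is constant, and no document says how the baseline correlation behaves. The 1-month visit lies inside the acute-toxicity window and near the start of chemotherapy, so it need not be the visit closest to baseline.
- That the treatment effect is biased. Randomisation makes baseline independent of arm, so with loss unrelated to outcome a wrong common slope costs efficiency only.
- That the participant-by-time term can only be a linear slope. Free covariance across visits is another reading.
- That intercept plus slope clearly inflates type I error. Under steadily changing SDs its size stays near or below nominal; material inflation needs an abrupt SD jump at 60 months.
- That the two harms add up. A rising SD shrinks the common-slope loss, while equal SDs make the intercept-plus-slope test conservative.

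**Conclusion.** The point holds as a cheap improvement to the model as written. It does not invalidate the analysis, and no stated sample size or power figure is wrong. The unadjusted t-test basis leaves a reserve: in the five tabulated cases, power with a common slope and unstructured covariance stays at or above the stated 89% or so, and only strong decay combined with intercept plus slope takes it to 86.8%.

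The common slope is a modest, conditional efficiency matter. The more serious matter is the intercept-only model that the wording permits: it is correct if correlation and variance are constant over visits, but otherwise the claimed family-wise control would fail. All sizes rest on assumed correlations and SDs, loss completely at random, and large-sample approximations.

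**What to change.** In the analysis plan, and in the protocol at its next amendment:

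1. State that timepoint is categorical.
2. Add a baseline NCF by timepoint interaction (six visit-specific slopes instead of one, so five extra parameters).
3. Replace the random effects by an unstructured within-participant covariance over the six post-RT visits (6 × 7/2 = 21 parameters, 246 participants), with Kenward-Roger degrees of freedom.
4. Name the 60-month contrast as the final test and the 24-month contrast as the Stage 2 test.
5. Prespecify the fallback if the model does not converge, for example heterogeneous Toeplitz with robust standard errors, and exclude random intercept only as a fallback.

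The cost is wording, a few parameters and some risk of non-convergence, which item 5 covers. No new data are needed. The secondary HRQoL and additional NCF analyses use similar models and can take the same wording.

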##### Secondary endpoints

Summary statistics by treatment arm at each timepoint will be presented for additional tests of NCF, HRQoL, caregiver distress, work and economic impact, treatment compliance, endocrinopathy and response assessment. Similar mixed-effects repeated measures models to those used for the primary endpoint will be used to compare HRQoL and additional NCF tests between treatment arms, adjusted for minimisation factors, relevant clinical characteristics and baseline HRQoL.

The numbers and proportions of participants experiencing each Common Terminology Criteria for Adverse Events (CTCAE) V.5.0 acute and late toxicity grade will be summarised.^27^ Safety data will be summarised using the safety population, with participants summarised according to the treatment they received. The proportion of participants experiencing serious adverse reactions and related unexpected serious adverse events will also be summarised.

Overall survival and progression-free survival will be analysed using Cox proportional hazards models. Kaplan-Meier and time to event estimates with 95% CIs will be presented.

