Adequate wound healing/recovery following surgery (if applicable)	Contraindication to MRI or gadolinium
Able to provide study-specific written informed consent	Severe active comorbidity making patient unsuitable for radical RT and/or adjuvant chemotherapy
Able to complete baseline NCF testing in English	Any recognised genetic syndrome causing sensitivity to RT
Adequate haematological, renal and hepatic function for PCV chemotherapy	Contraindication to procarbazine, lomustine or vincristine, including coeliac disease and rare hereditary conditions of galactose intolerance, total lactase deficiency or glucosegalactose malabsorption
Able to swallow oral medication	Prior invasive malignancy, unless disease-free interval ≥3 years
Participants born female of childbearing potential must agree to be pregnancy screened prior to entering the trial, provide a negative pregnancy result within 7 days prior to randomisation and agree to use medically acceptable methods of contraception during RT, between the end of RT and start of adjuvant chemotherapy, during chemotherapy and for 6 months following the end of chemotherapy	Pregnancy or breastfeeding
Fertile participants born male must agree to use medically acceptable methods of contraception during RT, between the end of RT and start of adjuvant chemotherapy, during chemotherapy and for 6 months following the end of chemotherapy	Participant unable or unwilling to attend for follow-up
	Recognised genetic syndrome causing sensitivity to radiotherapy

IDHisocitrate dehydrogenaseKPSKarnofsky Performance StatusNCFneurocognitive functionODGoligodendrogliomaPCVprocarbazine, lomustine and vincristine chemotherapyRTradiotherapy

**Table 2 T2:** Schedule of assessments

	Baseline/pretreatment			Treatment	Post-RT follow-up							
	Eligibility/preregistration	Prerandomisation	Pre-RT	Weekly RT	1 month	3 months	6 months	1 year	2 years	3 years	4 years	5 years
Medical history	X											
Clinical assessment	X			X	X	X	X	X	X	X	X	X
Pregnancy test	X	X	X		X	X	X					
Informed consent	X											
MRI scan	X		X			X	X	X	X	X	X	X
Radiotherapy planning CT scan			X									
PBT or photon RT				X								
PCV chemotherapy						6×6-weekly cycles of adjuvant PCV chemotherapy						
Neurocognitive function tests*		X			X			X	X	X	X	X
CTCAE toxicity assessment		X		X	X	X	X	X	X	X	X	X
Endocrine assessments			X				X	X	X	X	X	X
HRQoL†		X		X‡	X	X	X	X	X	X	X	X
Work and economic impact§		X		X‡	X	X	X	X	X	X	X	X
Caregiver distress¶		X		X*‡	X	X	X	X	X	X	X	X

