* EORTC core CTB COMP and CNS Vital Signs test battery.

† EORTC QLQ-C30 and BN20, EQ-5D-5L, MFI, HADS.

‡ Once in the final week of RT.

§ WPAI: General Health Questionnaire and health resource use questionnaire.

¶ Caregiver needs screen.

CNScentral nervous systemCTCAECommon Terminology Criteria for Adverse EventsEORTC CTB COMPEuropean Organisation for Research and Treatment of Cancer Core Clinical Trial Battery CompositeEORTC QLQ-C30 and BN20European Organisation for Research and Treatment of Cancer Quality of Life Questionnaire and Brain Neoplasm QuestionnaireEQ-5D-5LEuroQol-5 Dimension-5 Response-Level QuestionnaireHADSHospital and Anxiety Depression ScaleHRQoLhealth-related quality of lifeMFIMultidimensional Fatigue AssessmentPBTproton beam therapyPCVprocarbazine, lomustine and vincristineRTradiotherapyWPAIWork Productivity and Activity Impairment

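### The covariate list for the secondary models names baseline HRQoL as its only baseline score; read literally, CNS Vital Signs is not adjusted for its own pre-randomisation value

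*Protocol article*

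**What the plan says.** The sentence at issue is in the protocol article, Statistical analyses, Secondary endpoints. It opens with "Similar mixed-effects repeated measures models to those used for the primary endpoint" and says that these "will be used to compare HRQoL and additional NCF tests between treatment arms, adjusted for minimisation factors, relevant clinical characteristics and baseline HRQoL".

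Four other places bear on it:

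- **Primary endpoint (Statistical analyses):** "The model will adjust for minimisation factors, baseline NCF score, timepoint, treatment group and treatment group by timepoint interaction as fixed effects". The baseline term is that of the outcome being modelled.
- **Table 3:** the additional NCF tests are the "Computer-based CNS Vital Signs platform, which evaluates attention, psychomotor speed, verbal/visual memory and aspects of executive functioning".
- **Table 2:** the row "Neurocognitive function tests" is marked in the pre-randomisation column, then at 1 month and at years 1 to 5. Its footnote defines the row as "EORTC core CTB COMP and CNS Vital Signs test battery", so CNS Vital Signs is included.
- **Table 2, HRQoL footnote:** HRQoL means questionnaires only (QLQ-C30 with BN20, EQ-5D-5L, MFI, HADS).

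**The concern.** The list fits one of its two outcome families. For an HRQoL scale, baseline HRQoL naturally means the same scale before randomisation. For a computerised performance test it is a different kind of measurement. With several questionnaires in use, it is not even clear which score would be entered. Where the primary model has its own baseline NCF score, this sentence has baseline HRQoL, for the cognitive tests as well.

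If an analyst followed the list as written, the CNS Vital Signs models would leave out a measured pre-randomisation covariate that would usually be expected to predict the outcome well. The intervals would be wider than they need be, and a chance difference between arms in starting cognition would pass uncorrected into the estimate. These are two views of the same loss. The minimisation factors (grade, tumour size, extent of surgery, site, sex) include no cognitive measure, so the allocation does not control that difference directly.

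**Working it through.** **1. The plan's own figures.** No sample size, power or alpha is stated for CNS Vital Signs. The only stated figures concern the primary endpoint, and they reproduce. For effect size 0.5 at two-sided 5%, the noncentral t gives power 0.8999 with 85 per arm and 0.9032 with 86, so 86 per arm is right for 90%. Then 86 / (1 − 0.30) = 122.9, rounded up to 123 per arm, 246 in all. None of this depends on the secondary covariate list.

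**2. The two specifications side by side.**

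| Element | Primary model | Secondary models (HRQoL and CNS Vital Signs) |
|---|---|---|
| Minimisation factors | named | named |
| Baseline score | baseline NCF, the outcome itself | baseline HRQoL only |
| Clinical characteristics | not named | named, not defined |
| Timepoint, treatment, interaction | named | not repeated |
| Random effects | named | not repeated |

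The fourth and fifth rows show that the secondary sentence is not a complete specification, since a model comparing arms needs a treatment term. Some of it must be inherited from the primary model. The second row is different: there the sentence does not stay silent but names a baseline score, and that score suits only the HRQoL outcomes.

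**3. Is the matching baseline available?** Yes. The Table 2 row and its footnote, read together, place CNS Vital Signs before randomisation.

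**4. Illustrative size.** The article gives no correlations, so those below are assumptions. With one baseline covariate correlated r with the outcome, residual variance is (1 − r²) times the unadjusted variance.

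- Baseline HRQoL, r = 0.2: 1 − 0.04 = 0.96
- Own baseline, r = 0.5: 1 − 0.25 = 0.75; ratio 0.75 / 0.96 = 0.78, or 22% lower
- Own baseline, r = 0.6: 1 − 0.36 = 0.64; ratio 0.64 / 0.96 = 0.67, or 33% lower
- Own baseline, r = 0.7: 1 − 0.49 = 0.51; ratio 0.51 / 0.96 = 0.53, or 47% lower

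Interval width scales with the square root: √0.78 = 0.88 and √0.53 = 0.73, so intervals would be about 12% to 27% narrower.

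**5. Wider ranges.** With r = 0.1 to 0.3 for baseline HRQoL, the factor is 0.99 to 0.91 (1% to 9% of variance removed). With r = 0.5 to 0.8 for the own baseline, it is 0.75 to 0.36 (25% to 64% removed). The least favourable pairing gives 0.75 / 0.91 = 0.82, or 18% lower. The most favourable gives 0.36 / 0.99 = 0.36, or 64% lower.

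**6. The same in power terms.** Take 86 per arm, two-sided 5%, and an assumed effect of 0.3 unadjusted SD, with power = Φ(0.3 / √(2(1 − r²)/86) − 1.96). For r = 0.2: 0.3 / 0.149 = 2.01, giving 52%. For r = 0.5: 0.3 / 0.132 = 2.27, giving 62%. Over the wider ranges, power is 51% to 54% with baseline HRQoL and 62% to 91% with the own baseline.

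Steps 4 to 6 compare two one-covariate models. They ignore the minimisation factors, the clinical characteristics and the repeated measures, any of which could change the gain from adding the own baseline.

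**The case against.** The strongest reply is that the list cannot be exhaustive. As the table in the working shows, it omits even the treatment term, so the reader is meant to take the structure from the primary model. That structure includes the outcome's own baseline. On this reading, baseline NCF carries over for the cognitive tests and baseline HRQoL is simply its counterpart for the questionnaires. The reference to clinical characteristics is also open-ended and does not exclude baseline cognition. Exact covariates by outcome are ordinary analysis-plan content, and the article promises a detailed analysis document before any analysis.

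Much of this stands. A reader might infer that the trial will certainly analyse CNS Vital Signs without its own baseline. The article does not support that, because carry-over may well be intended.

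It does not remove the point. The sentence is not silent on the baseline score. It names one for both families, in the place where the primary model names its own, and no other part of the article corrects it. That is a statement that fits one outcome and not the other, rather than detail left for later. If it is a drafting slip, an analysis plan written from it could repeat the slip.

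**Conclusion.** The point holds as a mismatch in wording with a modest consequence. Read literally, the stated list does not adjust CNS Vital Signs for its own pre-randomisation score, although that score is collected and the primary model follows the own-baseline principle. What is at stake is precision, and protection against chance baseline imbalance, on a secondary endpoint.

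Three stronger conclusions should not be drawn:

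- **Bias.** Randomisation keeps the comparison unbiased in expectation under either covariate. One might suspect bias through the 30% loss assumed at 5 years, but the article does not say whether loss depends on starting cognition.
- **A corroborative role.** A reader might see CNS Vital Signs as the endpoint meant to confirm the primary result. The article lists it only among the secondary endpoints and gives it no such role.
- **A variance gain for this trial.** The 22% to 47% rests wholly on assumed correlations (0.5 to 0.7, against 0.2) in a simplified comparison. The direction needs only that the test correlates more strongly with its own baseline than with a questionnaire. The size is not an estimate for this trial.

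No stated sample size, power or significance level changes.

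**What to change.** In the Secondary endpoints paragraph of Statistical analyses, replace the closing reference to baseline HRQoL with *the baseline score of the respective outcome*. Spell out that this is the pre-randomisation CNS Vital Signs score for the additional NCF tests, and the pre-randomisation score of the same scale for HRQoL. Keep the minimisation factors and the clinical characteristics as they are. Carry the same wording into the statistical analysis plan before any comparative analysis.

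The cost is one phrase. No new data, visits or participants are needed, and no stated figure has to be recalculated.
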